#### *Secondary outcomes*

We will consider the following secondary outcome:

- Time to any type of preterm birth (spontaneous or iatrogenic, any cause). This is calculated by censoring the outcome of gestational age at 37 weeks to only include any preterm birth, and calculating survival models.

### 2.4.2. Possible explanatory variables

The main predictor is cervical length (CL) measured in millimetres.

Below is a list of the additional available explanatory variables for the IPD meta-analysis, these were assumed to provide a minimum set of variables that can be used as predictors in this analysis.

Note that most explanatory variables are not available in all studies.

**Table1. Predictors of gestational age in the model analysis for multiple pregnancies**

| Variable name  | Description                          | Values                            |
|----------------|--------------------------------------|-----------------------------------|
| Age_mother     | Mother's age                         | numeric                           |
| Nullipara      | Nullipara                            | 0=no; 1=yes                       |
| Hx_PTB         | History of preterm births            | numeric                           |
| Chorionicity   | Chorionicity in multiple pregnancies | 1=monochorionic;
2=dichorionic |
| CL             | Cervical length                      | [mm]                              |
| GA_measurement | Gestational age at CL measurement    | [weeks]                           |

Predictor selection among pre-specified clinically meaningful predictors will be guided by:

- Availability of data across studies (only predictors that are available for at least 50% of data points will be included)
- Descriptive analyses of association between predictor and outcome

In cases where multiple CL measurements are available per participant, we will select the measurement closest to 20 weeks gestation due to its proximity to the usual morphology ultrasound.

In addition, only CL measurements taken between gestational week 16 to 24 will be included in the analysis. In cases where only a range for gestational age at the time of measurement of the cervical length is provided for the entire individual study rather than individual level data, the mean of that range will be imputed as the gestational age.

All predictors will be specified before we start building models in our main analysis.

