### *IPD meta-analysis*

The primary outcome of interest for the analysis will be the association between CL measurement and the incidence of preterm birth. We will perform a two-stage IPD meta-analysis.

The first stage will comprise building regression models for each study, using all the explanatory variables available in each study. Correlations between multiples will be accounted for in the analyses. We will build cox proportional hazard models and present hazard ratios with 95% confidence intervals. We will build multiple models, as follows:

- 1) **Basic model including only cervical length as a predictor (Model 1) – primary model**
- 2) Model with only key demographic predictors (mother's age, nullipara) and cervical length (Model 2)
- 3) Model with all predictors in table 1 (Model 3)
- 4) Model with all predictors in table 1, only including studies that include all predictors (Model 4)

In the second stage, the results of the study-level regression models will be meta-analysed in a random-effects model. Forest plots will be presented for all models, and between-study heterogeneity will be determined using  $I^2$  statistic, between-study heterogeneity variance  $\tau^2$  and the prediction interval. Small study effect will be investigated with contour enhanced funnel plots.

We will present cumulative incidence curves to visualise Model 1.

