#### 4.6. Missing data

Given the aggregate nature of the data sets it is likely that there will be missing or not applicable variables between the studies. Multiple imputation is very difficult to perform for study-level missing data, instead the two-level meta-analysis described here will allow for outcome estimates using all the available variables in each study.

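### A study-level midpoint for gestational age at measurement is constant within the study, so it gives no adjustment in Models 3 and 4 and may admit the study to Model 4 under a label it does not meet

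*SAP*

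**What the plan says.** Section 2.4.2 lists "Gestational age at CL measurement" (GA_measurement, in weeks) as a Table 1 predictor and sets three rules that bear on it:

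- Availability: "only predictors that are available for at least 50% of data points will be included".
- Window: "only CL measurements taken between gestational week 16 to 24 will be included in the analysis".
- Imputation: if a gestational age range "is provided for the entire individual study rather than individual level data", then "the mean of that range will be imputed as the gestational age".

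Section 4.3 (IPD meta-analysis) describes a two-stage analysis: "The first stage will comprise building regression models for each study, using all the explanatory variables available in each study". Model 1, the primary model, contains CL only. Model 2 adds mother's age and nulliparity. Model 3 uses every Table 1 predictor. Model 4 is "Model with all predictors in table 1, only including studies that include all predictors (Model 4".

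Section 4.6 takes a different line on predictors that a whole study lacks: "Multiple imputation is very difficult to perform for study-level missing data", so each study contributes the variables it has. It does not mention the midpoint rule in 2.4.2.

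The SAP does not name the range-only studies or give their ranges. It does not say whether an imputed study has the predictor for Model 4 or for the 50% rule, or whether the window is tested on the midpoint or on the range limits.

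**The concern.** A covariate is imputed so that the model can adjust for it. In a per-study model, a value shared by all women in the study cannot do that. The rule therefore fills a column without adding information, and the filled column can decide two things: which studies enter Model 4, and whether GA_measurement passes the 50% threshold.

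What sets Model 4 apart from Model 3 is a common adjustment set across studies. If range-only studies enter it, its pooled hazard ratio mixes estimates adjusted for gestational age at the scan with estimates that are not, and the forest plot would not show which is which. The per-study description of CL against gestational age at measurement (4.3, Descriptive analyses) is also empty for such studies.

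The second issue is eligibility. The imputation sentence directly follows the window, so an analyst may apply the window to the imputed value. A midpoint does not show whether individual scans fell inside 16 to 24 weeks. Unlike the adjustment problem, this one could reach every model, including Model 1.

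**Working it through.** The SAP states no figure on this point, so there is none to reproduce. Three checks follow.

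**1. Constant covariate in a per-study Cox model.** Let x be CL and let c be the imputed value, equal for all women in the study. Each event contributes

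exp(βx_i + γc) / Σ_j exp(βx_j + γc) = exp(βx_i) / Σ_j exp(βx_j),

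because exp(γc) cancels. The likelihood does not depend on γ, and the estimate of β is the one obtained without gestational age. A numerical check with 400 simulated women and gestational age set to 20 for all gave a log partial likelihood of -677.1945 at γ = -1, 0 and +1, a Hessian of rank 1 out of 2, and zero variance for the covariate. This result needs no assumption beyond the SAP's own two rules.

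It follows that:
- Model 3: a range-only study gives the same CL estimate whether the midpoint is used or the variable is left out.
- Model 4: only membership can change.
- 50% rule: only the count can change. The 15 rows of Table 2 sum to 7,039, so half is 7,039 / 2 = 3,519.5, that is, 3,520 if one data point is one listed N. How many women have individual gestational ages is not stated.
- Models 1 and 2: no gestational age covariate, so no effect by this route.

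**2. How much the missing adjustment might matter (assumed inputs).** Two sets of simulations, with scans uniform over 16 to 24 weeks:

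*Set A.* CL with SD 8 mm, CL–gestational age correlation -0.3, true CL hazard ratio 0.951 per mm, one run of 8,000 women per setting.

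| Log HR per week of gestational age | CL HR without adjustment | CL HR adjusted |
|---|---|---|
| +0.05 | 0.946 | 0.951 |
| +0.10 | 0.946 | 0.954 |
| -0.05 | 0.953 | 0.949 |
| -0.10 | 0.962 | 0.952 |

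These are single runs, so the third decimal carries simulation error.

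*Set B.* CL shortening with gestational age, Cox model with delayed entry (which the SAP does not specify), six replicates of 20,000 women. Log HR per SD of CL, without versus with gestational age:
- 0.5 mm per week: -0.388 vs -0.398 (1 - 0.388/0.398 = 2.5%) and -0.575 vs -0.594 (3.2%).
- 1 mm per week: -0.346 vs -0.385 (10.1%) and -0.531 vs -0.593 (10.5%).

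The shift is modest in these settings. Its direction depends on what is assumed: either way in Set A, towards zero in Set B.

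**3. Midpoint against the window (assumed ranges, scans uniform within each range).** For a range from lo to hi, the share inside the window is [min(hi, 24) - max(lo, 16)] / (hi - lo).

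| Range (weeks) | Midpoint | Passes on midpoint | Share actually inside |
|---|---|---|---|
| 16–24 | 20 | yes | 8/8 = 100% |
| 18–22 | 20 | yes | 4/4 = 100% |
| 14–24 | 19 | yes | 8/10 = 80% |
| 14–26 | 20 | yes | 8/12 = 67% |
| 18–28 | 23 | yes | 6/10 = 60% |
| 20–30 | 25 | no | 4/10 = 40% |
| 11–20 | 15.5 | no | 4/9 = 44% |

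A range wholly inside the window is handled correctly. A range that crosses a limit is admitted or excluded as a block, and either can be wrong for a sizeable share of its women.

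**The case against.** The SAP never says that an imputed study counts as having GA_measurement. Section 2.4.2 itself separates a study-level range from individual data, and the references in 4.3 and 4.6 to variables available in a study can be read as observed data only. On that reading no range-only study enters Model 4. This stands as far as it goes: the mixing in Model 4 is what could happen, not what the SAP says will happen. It does not rescue the rule. If the imputed value does not count as available, it has no use in the regression models; if it does count, Model 4 is mislabelled.

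A reader might also infer that ineligible scans will enter the primary analysis. The documents do not support that. No range is given, the window is worded in terms of when measurements were taken, and nothing says that it is tested on the midpoint. The ranges tabulated above are illustrations.

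Nor is there support for saying that the midpoint rule biases the primary result through lost adjustment, since Model 1 does not adjust for gestational age and the subgroup and sensitivity analyses are built on Model 1. A general claim of bias towards zero fails as well, because the sign varies with the assumptions.

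Finally, removing every window-crossing study from the main models could be costly. A 15–24 week study would lose all its women although most may be eligible, and a single Table 2 study can be as large as 1,229 / 7,039 = 17% of the listed total. That argues for a sensitivity analysis, not outright exclusion.

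**Conclusion.** The point holds in this form. The midpoint rule cannot deliver the adjustment for gestational age that Models 3 and 4 claim in range-only studies; this is exact and follows from the SAP's own text. On the natural reading of the rule, such studies could also enter Model 4 and the 50% count, so that adjusted and unadjusted hazard ratios are pooled under one label. Section 4.6 points the other way, and the two sections need to be reconciled.

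The numerical effect on any pooled estimate cannot be established, because the number of range-only studies and their ranges are not stated. Under the assumed inputs the effect within one study was modest and of either sign.

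The window problem is conditional on two things that the SAP leaves open: that eligibility is checked on the midpoint, and that some range crosses 16 or 24 weeks. If every range-only study lies wholly within the window, only the Model 4 and 50% issues remain. Because the certain part concerns non-primary models and the part that could reach Model 1 is conditional, this is a should-fix.

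**What to change.** Replace the imputation sentence in 2.4.2 and align 4.3 and 4.6 with it:

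1. Where only a study-level range is known, GA_measurement is treated as missing for that study.
2. Model 3 is fitted there without it, and the forest plot marks the study as not adjusted for gestational age at measurement.
3. The study does not enter Model 4 and does not count towards the 50% rule.
4. The 16 to 24 week window is judged on the limits of the reported range, not on its midpoint. State how a study whose range crosses a limit is handled in the main analysis, and add to 4.5 a Model 1 sensitivity analysis that excludes such studies.
5. List the range-only studies and their ranges; the investigators hold this information.

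Cost: a few sentences in the SAP and one extra sensitivity analysis. Model 4 may lose some studies and have a slightly wider confidence interval. The Model 3 CL estimates from these studies do not change, so no information is lost there.

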### 3. Risk of bias assessment

QUIPS will be used to assess risk of bias. Each study will be assessed by two independent reviewers. Conflicts will be resolved in a consensus meeting or by consulting a third reviewer.

## 4. Statistical Analyses

### 4.1. Data

This analysis will combine data from the following 17 studies of mid-trimester transvaginal ultrasonographic cervical length measurement:

Table 2. Included studies

| Study            | Abbreviation | N    |
|------------------|--------------|------|
| Aboulghar et al  | Abo          | 193  |
| Arabin et al     | Ara          | 459  |
| Brizot et al     | Bri          | 318  |
| Fox              | Fox          | 1102 |
| Hofmeister et al | Hof          | 385  |
| Klein            | Kle          | 223  |
| Liem et al       | Lie          | 593  |
| Lim et al        | Lim          | 463  |
| Serra et al      | Ser          | 256  |
| Sperling et al   | Spe          | 383  |
| Aboulghar        | Abo2         | 199  |
| Weitzner         | Wei          | 103  |
| Pagani           | Pag          | 911  |
| Gyamfi-Bannerman | Gya          | 1229 |
| Seravalli        | Serv         | 222  |

## 4.2. Statistical significance

The statistical significance will be set at  $\alpha=0.05$  throughout the study.

## 4.3. Analysis methods

All analyses will be performed separately for studies of singleton and those of multiple pregnancies (use variable 'Multiples' to select studies), and these analyses will be published separately. This present statistical analysis plan is for the multiple analyses only.

Prior to conducting the analyses all data will be checked with respect to range, internal consistency, missing or extreme values, errors and consistency with published reports.

For any individual outcome there will be an a-priori decision whether the quality of data is sufficient to allow meaningful analysis. If this is not the case, the analysis will not be conducted, and this will be reported in the publication.

### *Descriptive analyses*

We will plot and tabulate the following analyses in a descriptive way:

- Characteristics of patients included in each study
- Distribution of measured CL in each study
- Relationship between measured CL and gestational age at CL measurement in each study
- Relationships between other included predictors and CL in each study

### *IPD meta-analysis*

The primary outcome of interest for the analysis will be the association between CL measurement and the incidence of preterm birth. We will perform a two-stage IPD meta-analysis.

The first stage will comprise building regression models for each study, using all the explanatory variables available in each study. Correlations between multiples will be accounted for in the analyses. We will build cox proportional hazard models and present hazard ratios with 95% confidence intervals. We will build multiple models, as follows:

- 1) **Basic model including only cervical length as a predictor (Model 1) – primary model**
- 2) Model with only key demographic predictors (mother's age, nullipara) and cervical length (Model 2)
- 3) Model with all predictors in table 1 (Model 3)
- 4) Model with all predictors in table 1, only including studies that include all predictors (Model 4)

In the second stage, the results of the study-level regression models will be meta-analysed in a random-effects model. Forest plots will be presented for all models, and between-study heterogeneity will be determined using  $I^2$  statistic, between-study heterogeneity variance  $\tau^2$  and the prediction interval. Small study effect will be investigated with contour enhanced funnel plots.

We will present cumulative incidence curves to visualise Model 1.

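### Model 4 is fitted in fewer studies than primary Model 1, so the difference between their pooled hazard ratios mixes adjustment with study selection

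*SAP*

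**What the plan says.** The IPD meta-analysis part of SAP section 4.3 sets out a two-stage analysis: a Cox model in each study, then random-effects pooling. It lists four models.

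- Model 1: "Basic model including only cervical length as a predictor (Model 1) – primary model". No study restriction is stated.
- Model 2: CL with mother's age and nulliparity. No study restriction is stated.
- Model 3: "Model with all predictors in table 1 (Model 3"). No study restriction is stated.
- Model 4: "Model with all predictors in table 1, only including studies that include all predictors (Model 4"). This is the only model with a restriction on studies.

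The first stage is described as "building regression models for each study, using all the explanatory variables available in each study". Section 4.6 repeats this as the answer to predictors that a whole study did not record: the two-stage approach "will allow for outcome estimates using all the available variables in each study". Section 2.4.2 warns: "Note that most explanatory variables are not available in all studies".

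A forest plot is planned for every model. Neither section 4.3 nor the sensitivity analyses for Model 1 in section 4.5 include a pooled CL-only fit limited to the Model 4 studies.

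**The concern.** Readers will see four pooled CL hazard ratios with increasing adjustment, and will naturally take the move from Model 1 to Model 4 as the effect of accounting for age, parity, history of preterm birth, chorionicity and scan timing. That move changes two things at once: the covariates and the studies. If the CL association varies between studies, which the planned random-effects model allows for, dropping studies can shift the pooled ratio when adjustment does nothing, or can hide a shift that adjustment does cause.

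What is at stake is the interpretation of the supporting models, namely whether CL keeps its predictive value once the other predictors are known. The primary estimate is not at stake.

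**Working it through.** **No planned figure to reproduce.** The SAP gives no event count, effect size, between-study SD (tau) or number of studies holding all predictors. The check therefore sets the model definitions side by side and then illustrates the size under stated assumptions.

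**Step 1. What changes between models.**

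| Comparison | Studies | Covariates |
|---|---|---|
| Model 1 to Model 3 | same | from none to whatever each study holds |
| Model 1 to Model 4 | all, then a subset | from none to all of Table 1 |
| Model 3 to Model 4 | all, then a subset | from mixed to all of Table 1 |

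No pair of pooled results holds the studies fixed while going from CL alone to full adjustment. In addition, section 4.6 deals only with predictors missing for a whole study. If a predictor is missing for some women within a study, those women may drop out of the adjusted fit but stay in Model 1.

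**Step 2. How many women Model 4 could keep.** Table 1 has five predictors besides CL. The 50% availability rule below Table 1 applies to each predictor separately. If each is available for a share *a* of women, the share with all five lies between max(0, 1 - 5(1 - *a*)) and *a*, and equals *a*^5 if availability is independent.

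| *a* | lowest | independent | highest |
|---|---|---|---|
| 0.5 | 0% | 3% | 50% |
| 0.8 | 0% | 33% | 80% |
| 0.9 | 50% | 59% | 90% |

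The rule therefore does not guarantee that Model 4 keeps a large part of the data.

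**Step 3. Chance shift from study selection, with no adjustment effect.** Inputs from the SAP: the 15 study sizes listed in Table 2, which sum to 7,039. (The text above that table says 17 studies; the 15 listed are used here.) Assumptions: hazard ratio 0.95 per mm, so log hazard ratio ln(0.95) = -0.0513; CL SD 8 mm; 30% of women with the event; within-study variance 1/(N × 0.30 × 64); *k* studies chosen at random for Model 4.

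*Between-study part only, equal weights:* SD of the shift = tau × sqrt(1/*k* - 1/15). With tau = 0.02 and *k* = 5: 0.02 × sqrt(0.2000 - 0.0667) = 0.02 × 0.365 = 0.0073. Relative to 0.0513 this is 14%.

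*With sampling error and the Table 2 sizes:* simulation of the random-effects estimate in *k* studies minus that in all 15, 4,000 runs per setting.

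| Setting | SD of shift, % of log hazard ratio | Runs with a shift above 20% |
|---|---|---|
| tau 0.02, *k* = 5 | about 17% (SD 0.0088) | 23% to 25% over repeated simulations |
| tau 0.01 to 0.03, *k* = 4 to 8 | about 7% to 27% | 1% to 47% |
| tau 0.01 to 0.03, *k* = 10 | about 5% to 12% | not tabulated |
| *k* = 15 | 0% | 0% |

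**Step 4. After the fix.** If Model 1 is also pooled in the Model 4 studies and women, both estimates use the same *k* studies and the term tau × sqrt(1/*k* - 1/15) drops out. The remaining difference is due to adjustment, including the non-collapsibility of the hazard ratio: adding a prognostic covariate changes a hazard ratio even without confounding.

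**The case against.** The strongest reply is that the SAP does not plan the comparison criticised here. It lists four models, names Model 1 as primary, and specifies no change-in-estimate analysis. Section 2.2 gives the aim as whether CL predicts spontaneous preterm birth, not whether it does so independently of the other predictors. This stands: the difficulty lies in how the results will be read, not in a test that the plan prescribes.

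Second, the analysis is two-stage, so Model 1 is fitted in every Model 4 study. With a forest plot for each model, the unadjusted and adjusted ratios of each such study would normally both be visible, and a reader could re-pool them. This stands in part. It would be wrong to say that no unadjusted fit exists in those studies. What is missing is a pre-specified pooled result for that subset, and an assurance that the same women enter both fits.

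Third, Models 3 and 4 act as a partial sensitivity pair, because in studies holding every predictor their first-stage fits coincide. That gives some information on study selection, but it is mixed with the varying adjustment in the other studies.

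A reader might also infer that Model 3 is fitted in a different set of studies from Model 1. The text does not support that: sections 4.3 and 4.6 keep each study in Model 3 with the variables it has. The weakness of Model 3 is its mixed adjustment sets.

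Finally, the numerical illustration rests on assumed values. Even the 17% case (SD 0.0088) corresponds to a 95% spread of exp(-0.0513 ± 1.96 × 0.0088), or about 0.934 to 0.967 per mm around 0.95, all in the same direction.

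**Conclusion.** The point holds for Model 4 and is modest in weight. By its definition Model 4 uses only studies with every Table 1 predictor, and section 2.4.2 indicates that this will exclude studies. The pooled Model 1 and Model 4 hazard ratios therefore differ in adjustment and in study set together, possibly also in which women are included. Model 3 does not resolve this, because its pooled ratio combines fully, partly and barely adjusted estimates.

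The size is not known. Under the assumptions in the working, the study-selection shift has an SD of about 7% to 27% of the log hazard ratio with 4 to 8 of 15 studies, less with more studies, and zero if all studies hold all predictors. These figures take the Model 4 studies as a random subset; studies that record every predictor may also differ systematically.

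A reader might conclude that the primary result is biased, or that the SAP commits to a faulty comparison. The document supports neither. Model 1 is unaffected, and the fault appears only when the pooled models are set beside one another. The change is worth making because it is cheap and removes the ambiguity.

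**What to change.** Add to section 4.3, after the list of models:

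> Models 1 and 2 will also be fitted and pooled in exactly the studies and women used for Model 4. The effect of adjustment will be read from this common set, and the number of studies and women behind each model will be reported.

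The report should note that the remaining difference includes non-collapsibility of the hazard ratio, so it should not be read as confounding alone.

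Two further steps are optional: labelling Model 3 as descriptive, and pooling the unadjusted and fully adjusted log hazard ratios jointly in a bivariate random-effects model, so that studies without all covariates still contribute. The second would need the within-study covariance of the two estimates.

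The main change costs two sentences and one extra set of fits on data already held. It does not alter the primary analysis.

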#### 2. Study Overview

##### 2.1. Background and introduction

Preterm birth is in quantity and severity the most important issue in obstetric care in the world. In Australia, preterm delivery occurs in approximately 8.6% of all deliveries, while these rates rise to 63% for multiple pregnancies. Preterm delivery can either be iatrogenic (i.e. medically indicated) or spontaneous, with iatrogenic preterm birth being 3.9% and spontaneous onset being 4.7% of all deliveries in 2013.

Spontaneous preterm birth is linked to adverse outcomes, including increased risk of infant mortality and severe morbidity, and is associated with an increased risk of spontaneous

preterm birth in a subsequent pregnancy. Prevention of spontaneous preterm delivery is therefore a major perinatal research priority.

A preventative strategy for spontaneous preterm birth is dependent on the identification of high-risk women and the effectiveness of subsequent treatment. Potential treatments include cerclage, pessary and progestogens, while aspirin (certain) and dietary interventions (likely) are also effective.

The focus of this project is on the identification of high-risk women for spontaneous preterm delivery. Over the last decades, many studies have been performed to address prediction of spontaneous preterm birth. However, coordination of these efforts has been lacking and therefore research resources have been used suboptimally. To allow optimal use of current data, the best type of evidence synthesis is individual participant data (IPD) meta-analysis.

Background, rationale and general methodology of the IPPIC-II project have been documented in the grant proposal.

Previous evidence suggests that mid-trimester transvaginal ultrasonographic cervical length (CL) measurement may be an important predictor of spontaneous preterm birth. This statistical analysis plan sets out the analyses for an IPD meta-analysis assessing the value of mid-trimester transvaginal ultrasonographic CL measurement in predicting preterm birth. The plan proposes a method of quantifying changes in the probability of preterm birth, accounting for mid-trimester cervical length among other potential effects.

These methods have been selected to best allow for the effects to be incorporated into future decision support tools.

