## 2.4. Variables of interest

### 2.4.1. Outcomes

#### *Primary outcome*

The primary outcome is gestational age in weeks at spontaneous preterm birth (time-to-event outcome). This is calculated by censoring the outcome of gestational age at 37 weeks to only include spontaneous preterm births, and calculating survival models. Studies that also reported medically indicated preterm birth, are treated as censored observation.

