#### 4.5. Sensitivity analyses

We will conduct the following sensitivity analyses for Model 1:

- Exclude women that receive treatment for preterm birth (Cerclage, Progesterone, Pessary), time-to-event
- Spontaneous PT birth (<37 weeks), binary outcome
- Spontaneous PT birth (<34 weeks), binary outcome
- Spontaneous PT birth (<30 weeks), binary outcome
- Exclude studies with an overall high risk of bias

We will build logistic regression models for binary outcomes, and present results as odd ratios with 95% confidence intervals. In addition, the non-linear association between cervical length and preterm birth will be investigated with generalised additive models such as splines.

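### Cumulative incidence curves tied to a Cox model that censors medically indicated births will overstate the absolute risk of spontaneous preterm birth, unless a competing-risk estimator is specified

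*SAP*

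**What the plan says.** Section 2.4.1 of the SAP defines the primary outcome as time to spontaneous preterm birth, with follow-up ending at 37 weeks: "This is calculated by censoring the outcome of gestational age at 37 weeks to only include spontaneous preterm births, and calculating survival models". On indicated births it says: "Studies that also reported medically indicated preterm birth, are treated as censored observation". The grammar is loose, but the evident sense is that an indicated preterm birth is censored.

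Section 4.3 (IPD meta-analysis) fits the models to this outcome: "We will build cox proportional hazard models and present hazard ratios with 95% confidence intervals". The primary one is listed as "Basic model including only cervical length as a predictor (Model 1) – primary model". The absolute-risk display follows from it: "We will present cumulative incidence curves to visualise Model 1".

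Section 4.5 adds logistic models for spontaneous birth before 37, 34 and 30 weeks, for example "Spontaneous PT birth (<37 weeks), binary outcome" and "Spontaneous PT birth (<34 weeks), binary outcome". It does not say how an indicated birth before the cut-off is coded.

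Section 5 lists spontaneous and indicated preterm birth as separate 0/1 variables, with gestational age at delivery. The SAP nowhere names a competing-risk method.

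**The concern.** Censoring assumes that the woman could still have the event after she leaves the risk set. For a cause-specific hazard ratio that does no harm, because the hazard concerns only women still pregnant. For an absolute risk it matters. One minus survival from a model that censors indicated births shares those women's later risk among the women who remain, as if they could still go into spontaneous preterm labour. The result is the risk in a hypothetical world without indicated delivery.

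The SAP's background section says that the plan will quantify changes in the probability of preterm birth, and that the methods were chosen with future decision support tools in mind. The Model 1 curves are the only time-to-event display of absolute risk in the plan. A reader will take their height as the probability of spontaneous preterm birth at a given cervical length. Indicated birth can often be ignored when it is rare, but in a twin population it is not.

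**Working it through.** The SAP gives no absolute-risk figure for this point, so there is nothing to reproduce. The calculation below shows size only.

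**Inputs (SAP section 2.1)**
- Preterm birth in multiple pregnancies: p = 0.63 ("while these rates rise to 63% for multiple pregnancies").
- Spontaneous 4.7% and iatrogenic 3.9% of all deliveries, 8.6% in total. Spontaneous share s = 4.7/8.6 = 0.547.
- Assumptions: the all-deliveries split holds in twins, and the two cause-specific hazards are proportional over time.

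**Formulas**
- Real cumulative incidence of spontaneous birth (what Aalen-Johansen estimates): p × s.
- Total cumulative hazard: −ln(1 − p). The spontaneous part is s times this, so with indicated births censored, 1 minus survival = 1 − (1 − p)^s.

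**Base case at 37 weeks**
- Real: 0.63 × 0.547 = 34.4%.
- Censoring-based: 1 − 0.37^0.547 = 41.9%.
- Excess: 7.5 points, ratio 1.22.

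**Varying the rate and the spontaneous share** (real → shown at 37 weeks)

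| Total preterm | share 0.40 | share 0.547 | share 0.70 | share 0.80 |
|---|---|---|---|---|
| 40% | 16.0 → 18.5 | 21.9 → 24.4 | 28.0 → 30.1 | 32.0 → 33.6 |
| 50% | 20.0 → 24.2 | 27.3 → 31.5 | 35.0 → 38.4 | 40.0 → 42.6 |
| 63% | 25.2 → 32.8 | 34.4 → 41.9 | 44.1 → 50.1 | 50.4 → 54.9 |

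The excess runs from 1.6 to 7.6 points (ratio 1.05 to 1.30). At the all-deliveries rate of 8.6% it is only 0.1 point (4.7% against 4.8%).

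**Varying the timing** (63%, share 0.547)
- Bounds at 37 weeks: no excess (34.4%) if every indicated birth follows every spontaneous one. If all precede them, the curve shows 0.344/(1 − 0.286) = 48.2%, where 0.286 = 0.63 × 3.9/8.6.
- Simulation of 400,000 women, with delivery times drawn as 20 + 17 × Beta(a, 1) weeks:
  - Same timing for both causes (a = 3): 7.0% real against 7.3% shown at 30 weeks (excess 0.2 points before rounding), 19.4% against 21.3% at 34 weeks, 34.5% against 42.0% at 37 weeks.
  - Indicated births later (a = 5 or 8, spontaneous a = 3): the 37-week excess falls to 5.9 or 4.5 points, and at 30 weeks it is 0.1 point or less.
  - Indicated births earlier (a = 3, spontaneous a = 5): the 37-week excess rises to 9.1 points (34.5% against 43.6%).

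**Binary outcome before 37 weeks** (base case)
- Indicated births kept as non-events: 34.4%, equal to the real risk.
- Indicated births excluded: 0.344/(1 − 0.286) = 48.2%, further from the real risk than the 41.9% curve.

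**The case against.** The strongest reply is that the SAP does not say 1 minus survival. Cumulative incidence is also the usual name for the Aalen-Johansen quantity, and the analysts may intend that. This stands, and it makes the point conditional. It does not remove it: the only model to which the text ties the curves is the one that censors indicated births.

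A reader might infer more than the SAP supports:

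- **That the primary result is wrong.** It is not. The Model 1 hazard ratio, its forest plot, its heterogeneity statistics and its prediction interval do not depend on the curve estimator. The secondary outcome of any preterm birth has no such competing event.
- **That the logistic analyses miscode indicated births as non-events.** Section 4.5 states no coding. Non-event coding would in any case be the right match: at a fixed cut-off it has the same target as an Aalen-Johansen curve.
- **That some studies would count indicated births as events.** Nothing in the SAP shows that any study in Table 2 cannot separate the type of onset, and spontaneous birth has its own variable in section 5.
- **That a two-stage analysis cannot yield curves.** Section 4.3 promises no single pooled curve, and individual data allow curves within study.

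It is also fair to say that the base case is not neutral. The split comes from all deliveries, and later indicated births would shrink the excess.

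**Conclusion.** The concern holds for the absolute-risk display and should be fixed there. If the curves are drawn from Model 1 with indicated births censored, they lie at or above the real probability of spontaneous preterm birth.

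The likely excess at 37 weeks is about 2 to 8 points over plausible rates and shares, and 7.5 points in the base case. It is smaller if indicated births come later, larger if they come earlier, and small at 30 weeks. These figures rest on the background rate of 63% and on an assumed twin split. The range over rates and shares also assumes proportional cause-specific hazards. They describe an overall curve. The SAP gives no risks by cervical length, so the excess within a band cannot be computed from it.

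The hazard ratios are unaffected, so this does not threaten the primary analysis.

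**What to change.** - **Section 4.3.** State that the curves are Aalen-Johansen cumulative incidence curves by cervical length band, with indicated birth as a competing event. Alternatively, build them from two cause-specific Cox models on cervical length, one for spontaneous and one for indicated birth, which keeps the link to Model 1. Say whether they are shown within study or combined, and by what method. Label the Model 1 hazard ratio as cause-specific.
- **Section 4.5.** Keep the three logistic models. State that indicated births before the cut-off stay in the denominator as non-events, and do not exclude them.

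The cost is SAP wording and standard R functions. The variables needed (spontaneous birth, indicated birth, gestational age at delivery) are already in section 5. The displayed risks will be lower than under censoring, and studies that did not record indicated births may be unable to contribute to the curves.
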